### Process evaluation

Results of the questionnaires for the process evaluation of participants and nurses will be analyzed descriptively. A summary score of MI fidelity will be computed by ratings of the MI-consistent behavior evaluated by the MITI. Summary score thresholds are known for beginning proficiency level and competency level [94]. A binary variable MI fidelity will be computed and used in analyses for the effectiveness of MI as well as working mechanisms of MI. MI fidelity is furthermore used in mediation analyses as hypothesized mediator in the path between the MI intervention and its effect.

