#### PREPARE conditions

The PREPARE intervention focuses on phase one. This is also the period during which patients are waiting before they can start their actual treatment (observation and rehabilitation treatment). During the study, patients will receive either the new MI-based intervention or care as usual. In order to standardize treatment options, both arms (MIP as well as UC) will include two sessions with identical contact time. In order to prevent contamination of treatment, each treatment condition will be delivered by different nurses. Figure 1 illustrates the situation during the PREPARE study.

1. Usual care (UC)

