#### Nurses

Both UC and MIP are administered by registered nurses working in the field of rehabilitation. In order to prevent contamination of treatment by components of the other intervention, nurses will be trained and only guide participants in one specific condition. The two nurses selected to deliver the MI condition, are both experienced MI coaches (4 years of experience). To assure optimal quality of the MI condition, both nurses receive an expert training by a certified MI trainer: their MI knowledge and experience in the context of chronic pain rehabilitation are updated based on an evidence-based training tailored to their specific needs [45-49]. During the study the MI sessions will also be audio taped and the MI quality will be assessed using a coding instrument (Motivational Interviewing Treatment Integrity (MITI)) (see also Methods section, Process evaluation section). Subsequent training will be based on additionally regular supervision, done by training on the job and direct feedback on MIP sessions.

Quality of the UC condition:

The two nurses selected to deliver the usual care condition are experienced in the field of rehabilitation (20 years and 5 years, respectively).

Before the start of the study, they will receive a 3-h refresher training in general communication skills and general principles of health education. In addition, the content of relevant chapters of the book ‘Mastering pain’ is discussed. During the study, the nurses of the UC condition will meet once or twice a year to discuss problems encountered during the sessions.

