#### Process evaluation: MI integrity and MI fidelity

To check whether MI was implemented and delivered as intended, an evaluation of treatment fidelity and treatment integrity is important.

Also given the explicit emphasis in MI as a spirit rather than a technique [93], treatment fidelity and treatment integrity will be measured. Therefore, the MI Treatment Integrity Code (MITI version 3.1) [94] will be used. It has shown to be a cost-effective and reliable tool [95,96], which is also validated to check MI fidelity [94,97]. Feedback during the training and during intervision sessions will be delivered based also on the MITI. Research has also shown that proficiency rating by skilled coders predicted treatment outcome [98-100]. To be able to do so, all pre-treatment sessions are audio taped, and a random sample of 20% of all sessions will be scored by one of the authors ([name]). Twenty per cent out of those will also be scored by another skilled coder (NN) using the abovementioned MITI instrument.

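### The graded MITI fidelity score is cut to a binary variable before it is related to effectiveness and working mechanisms; keeping it continuous would normally save information at almost no cost

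*Protocol article*

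**What the plan says.** The Process evaluation paragraph under Statistical analysis builds the fidelity variable in steps. First, "A summary score of MI fidelity will be computed by ratings of the MI-consistent behavior evaluated by the MITI". Next it notes that "Summary score thresholds are known for beginning proficiency level and competency level". Then comes the choice at issue: "A binary variable MI fidelity will be computed and used in analyses for the effectiveness of MI as well as working mechanisms of MI". A last sentence adds mediation: "MI fidelity is furthermore used in mediation analyses as hypothesized mediator in the path between the MI intervention and its effect". That sentence does not say whether the score or its binary version is meant.

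The section on MI integrity and MI fidelity sets the amount of data: "a random sample of 20% of all sessions will be scored by one of the authors". The section on the PREPARE conditions says that "both arms (MIP as well as UC) will include two sessions with identical contact time". According to the Nurses section, two nurses deliver MIP. Both are experienced in MI, trained by an expert, and supervised with feedback during the trial.

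The article gives no distribution for the summary score, no expected share of sessions above either threshold, and no power or precision for the fidelity analyses.

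**The concern.** The plan creates a graded measure of delivery quality and then replaces it with a yes/no variable in the analyses that relate fidelity to effect. A session just above the cut is treated like an excellent one, and a session just below it like a poor one. When outcome changes gradually with quality, this discards information, and it discards more as the split becomes more uneven.

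The matter is not trivial to this trial's aims. The article treats MI integrity as a hypothesised working mechanism, and its Discussion says fidelity is checked partly to help interpret the MI effect. What is at stake is the precision of those secondary analyses, which already rest on few scored sessions.

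**Working it through.** **The plan's own figure.** The only sample-size figure concerns the primary outcome. With a difference of 5, an SD of 10, two-sided α = 0.05 and 80% power, n = 2 × (1.960 + 0.842)² / 0.5² = 62.8, so 63 per arm by the normal approximation. The t-test calculation gives 63.8, so 64 per arm and 128 in total. Then 128 / 0.80 = 160. The stated figures are reproduced, and nothing below changes them.

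**Number of scored sessions.** Two sessions each for 160 participants make 320, and 20% of these is 64. For MIP alone, 80 × 2 × 0.20 = 32. This assumes that everyone attends both sessions.

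**Information kept by a binary cut.** The measure is the squared correlation between the score and its binary version, which is the relative efficiency when the effect is linear. Let p be the share passing, z the matching normal quantile and φ the normal density.

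- Normal score: φ(z)² / [p(1 − p)]
- Uniform score: 3p(1 − p)

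| Share passing (assumed) | Normal: kept | Normal: lost | Uniform: lost | 32 MIP sessions worth (normal) |
|---|---|---|---|---|
| 50% | 0.637 | 36% | 25% | 20 |
| 80% | 0.490 | 51% | 52% | 16 |
| 90% | 0.342 | 66% | 73% | 11 |
| 95% | 0.224 | 78% | not needed | 7 |

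Example for the 80% row, normal score: z = 0.842 and φ(z) = 0.280, so 0.280² / (0.8 × 0.2) = 0.49.

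**Other shapes.** Suppose both arms are pooled and their scores lie 3 to 4 SD apart. A cut midway between the arms then loses 25% to 19%, while a cut at the MIP mean loses 46% to 48%. If the true relation is a step exactly at the threshold, the binary variable loses nothing.

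**Effect on power.** Assume a true correlation of 0.3 between score and outcome and 32 scored sessions treated as independent. This is optimistic, since two nurses deliver them. By the Fisher z approximation, power = Φ(atanh(r) × √29 − 1.96):

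- continuous score, r = 0.30: 38%
- median cut, r = 0.30 × √0.637 = 0.239: 26%
- 80/20 cut, r = 0.30 × √0.490 = 0.21: 21%

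**The case against.** The best defence is that a threshold variable has a rationale here. The article wants to check that MI was delivered as intended and calls fidelity a prerequisite for effects, and a prerequisite is naturally either met or not. The cut points come from the instrument, not from the trial data. This stands as a reason to report the thresholds, and it is why the loss is nil under a true step. It is not a reason to leave the graded score out of the outcome analyses, because the article nowhere claims a step.

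A second objection is that the fix changes little. Sampling 20% of sessions from two nurses limits these analyses more than the cut does, and 38% power is poor too. If trained nurses all score high, the continuous score will also vary little. This is fair, and it keeps the point minor.

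A reader might also infer three stronger things that the article does not support:

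- **That the outcome hangs on which of two thresholds is chosen.** The article says only that thresholds are known. The operative cut may be fixed in a full plan that is not shown, so its absence is no finding. How much the choice matters depends on unknown pass rates: if 80% pass the lower cut and 50% the upper, 30% of sessions change class; if 95% and 90% pass, 5% do.
- **That nearly all MIP sessions will pass, leaving the analysis almost uninformative.** The nurses' experience makes high pass rates plausible, but no rate is given. This inference also works against the previous one, since sessions that pass both cuts are not reclassified.
- **That every fidelity analysis uses the binary form.** The mediation sentence leaves this open.

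**Conclusion.** The point holds as a minor improvement to secondary and process analyses. The article makes a positive choice to use a binary variable and states no analysis of the score against outcome, although the score is already computed.

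The size of the loss is conditional. For a roughly normal score with a linear effect it is about 36% at a median cut and rises with imbalance. It is wrong to read a loss of at least a third as a general floor: a uniform score cut at its median loses 25%, well-separated pooled arms can lose 19%, and a true step loses nothing. The larger losses (51% to 78%) rest on assumed pass rates of 80% to 95%. The primary comparison and the sample size are untouched.

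**What to change.** In the Process evaluation paragraph, name the continuous MITI summary score as the main fidelity variable in every analysis relating fidelity to outcome, and say that the mediation analysis uses it too. Use the two thresholds for hypothesis 3, by reporting the share of MIP sessions reaching beginning proficiency and the share reaching competency. If a binary version is kept, label it supplementary, name its cut in advance, and report the other cut as a sensitivity analysis.

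The cost is one changed line of analysis wording and a result that reads less directly as met or not met. No extra data or coding is needed.

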### Sample size

The sample size calculation is based upon an estimated difference in change in level of participation between baseline and 6-month follow-up (after completion of the rehabilitation treatment) as assessed by the Utrecht Scale for Evaluation of Rehabilitation-Participation (USER-P) [35,36]. Reproducibility [37], responsiveness [38], and validity [37] of the USER-P are satisfactory. As participation is the important outcome in rehabilitation, we have chosen this as primary outcome. The scale consists of the three aspects of participation represented by the subscales Frequency, Restriction, and Satisfaction. The sum score of each subscale is converted to scores on a scale ranging from 0 to 100. There is no USER-P total score.

Our sample-size calculation is based upon the subscale Satisfaction. This subscale is the most important part of participation as it marks the subjective experience of participation [9]; therefore we have chosen this one.

As at this moment no information is available about the USER-P in a pain population regarding normative values, clinically relevant change, and clinically relevant difference, our study is exploratory of character. In a study by van der Zee (2011) the USER-P is taken in different patient groups at three different points in time [38]. As these groups were part of a cohort study, nothing is known about differences after a specific treatment. We know from other studies that multidisciplinary pain rehabilitation treatment is moderately effective with effect sizes ranging from 0.30 for behavioral outcomes up to 0.40 for functional outcomes [14]. We expect an additional effect for the MIP intervention since systematic reviews of motivational interviewing-based interventions show an effect size ranging from 0.27 up to 0.40 when compared with a weak comparison group [30-32,39]. It has to be said that in those reviews no study in the field of chronic pain or rehabilitation treatment was taken into account. Therefore, our power calculation is based on the following two assumptions:

1. Using an expected mean change of 5 points within UC is expected whereas a difference of additional 5 points (thus at least 10 points in total) within MIP in the USER-P sub scale Satisfaction is considered as clinically relevant. Those numbers are estimates as the clinically relevant difference is not known yet.

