2. Assuming a standard deviation of 10 points in both groups, the standardized effect size, Cohen’s d, is (10–5)/10 = 0.5 indicating a medium additional effect size of the MIP [40].

Assuming power (1-β) of 80%, α = 0.05, two-sided testing, and holding the above mentioned assumptions, would necessitate *n* = 128 participants (*n* = 64 per arm). With an expected total drop-out of 20% (10% drop-out from the study, another 10% drop-out during the usual rehabilitation treatment as our unsystematic registration has shown), *n* = 160 (*n* = 80 per arm) was chosen as the optimal total sample size. Additionally, as the recruitment of 160 participants in the region of South-Limburg/the Netherlands is feasible in a time range of 18 months, we have chosen for this amount of participants.

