#### MI-specific possible active ingredients

Resulting from the existing literature on MI, potential specific active ingredients were identified and will be assessed in this study [75,76].

The stage of change is assessed by the Multidimensional Pain Readiness to Change Questionnaire 2 (short version). It measures the chronic pain participants’ readiness to change. The questionnaire is based upon the trans theoretical model of behavior change of Prochaska and DiClemente. The MPRCQ2-26 consists of 26 items and is scored on a seven-point Likert scale [77]. Psychometric properties are evaluated and appeared to be satisfactory [78]. To be able to take it into account as possible moderator, it is measured before and after the pre-treatment.

MI integrity is hypothesized to be another working mechanism for MI. It is further explained below under the heading ‘MI integrity and fidelity’.

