### Moderation analysis

As secondary analyses, the working mechanisms of MI are investigated. For testing moderation, an interaction term of the potential moderator is constructed and analyzed by linear regression.

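### MI fidelity, scored in 20% of sessions and closely tied to arm, would be uninformative as a mediator, and readiness to change needs a fixed role and time point

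*Protocol article*

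**What the plan says.** All places are in the protocol article.

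- **Fidelity as mediator.** The Process evaluation part of the statistical analysis reduces the MITI ratings to a yes/no variable. It uses this variable in the effectiveness and mechanism analyses and adds: "MI fidelity is furthermore used in mediation analyses as hypothesized mediator in the path between the MI intervention and its effect".
- **Scoring.** The section on MI integrity and MI fidelity has all pre-treatment sessions taped, but "a random sample of 20% of all sessions will be scored". One fifth of those are scored a second time by another coder.
- **Who delivers what.** The Nurses section gives each nurse one condition only. The two MIP nurses have four years of MI coaching behind them and receive expert training and supervision. The two UC nurses receive a three-hour refresher on communication and health education. Table 1 gives UC fixed educational content without feedback.
- **Readiness to change.** Stage of change (MPRCQ2) stands among the potential active ingredients, both in the text and in Table 2. The text says of it: "To be able to take it into account as possible moderator, it is measured before and after the pre-treatment".
- **Moderators.** The Possible moderators section describes them as individual factors measured at baseline. The Moderation analysis section says: "For testing moderation, an interaction term of the potential moderator is constructed and analyzed by linear regression". It fixes no time point for the moderator.

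**The concern.** A mediator has to be observed in the patients who are analysed, and it has to vary within arm. Otherwise its effect on outcome cannot be told apart from the effect of arm. Fidelity does poorly on both counts: most patients have no score, and the design aims to make fidelity high in MIP and absent in UC. The better the trial is run, the closer the mediator comes to the allocation itself.

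Readiness raises a different problem. MIP is meant to raise it, so its T1 value is a possible consequence of treatment. An arm-by-T1 interaction compares groups formed after randomization and cannot be read as showing for whom MI works.

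The article promises insight into working and moderating mechanisms. A null fidelity result would be uninformative, and a T1 interaction could mislead.

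**Working it through.** **1. The plan's own figure.** Inputs from Sample size: "Assuming power (1-β) of 80%, α = 0.05, two-sided testing"; "a difference of additional 5 points (thus at least 10 points in total) within MIP"; "Assuming a standard deviation of 10 points in both groups".

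- Normal approximation: n per arm = 2 × (1.96 + 0.84)² × (10/5)² ≈ 62.8, so 63.
- The exact t-test gives 63.8, so 64 per arm and 128 in total.
- With 20% drop-out, 128/0.80 = 160. The stated 128 and 160 reproduce.

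**2. Patients with a fidelity value.**

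- Sessions: 160 × 2 = 320. Scored: 0.20 × 320 = 64. Scored twice: 0.04 × 320 = 12.8, about 13.
- Chance that neither session of a patient is drawn: (256/320) × (255/319) = 0.639.
- Patients with any score: 160 × (1 − 0.639) ≈ 58 (36%), about 29 per arm.
- Patients with both sessions scored: 160 × (64/320) × (63/319) ≈ 6.
- Among 128 evaluable patients (51 of 256 sessions scored): about 46 with any score, 23 per arm.

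**3. Overlap with arm, and power.** The article gives no pass rates, so the following are assumptions. Let *a* be the share passing the threshold in MIP, *b* the share in UC, q = (a + b)/2, and m the number of scored patients per arm.

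- Correlation of fidelity with arm: phi = (a − b) / (2√(q(1 − q))).
- Variance inflation: VIF = 1/(1 − phi²).
- Standard error of the fidelity effect adjusted for arm: SE = 10 / √(2m·q(1 − q)(1 − phi²)).
- Power ≈ Φ(5/SE − 1.96).

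The 5 points and the SD of 10 are borrowed from the sample-size section as a yardstick.

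| Pass rates MIP / UC | phi | VIF | Discordant with arm, of 58 | Power, 29 per arm | Power, 23 per arm | Power if all 64 per arm were scored |
|---|---|---|---|---|---|---|
| 70% / 10% | 0.61 | 1.6 | 11.6 | 31% | 26% | 59% |
| 80% / 5% | 0.76 | 2.4 | 7.2 | 23% | 19% | 45% |
| 90% / 5% | 0.85 | 3.6 | 4.3 | 17% | 14% | 32% |
| 95% / 0% | 0.95 | 10.5 | 1.5 | 8% | 8% | 14% |

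Worked line for 90% / 5% with 29 per arm: q = 0.475; phi = 0.85/(2 × 0.499) = 0.851; SE = 10/√(58 × 0.249 × 0.275) ≈ 5.0; power = Φ(5/5.0 − 1.96) ≈ 17%.

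The last column shows that scoring every session would not remove the problem, because the overlap with arm remains.

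**4. Other readings of the fidelity variable.**

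- The Nurses section mentions taping of the MI sessions. If only MIP sessions were coded, UC would have no value and mediation of the arm effect could not be estimated.
- If fidelity were a score per nurse, every patient would have a value. But the four nurses are nested in arm: if both MIP nurses pass and both UC nurses fail, fidelity equals arm.

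**5. Readiness, passages side by side.** Table 2 lists MPRCQ2 as an active ingredient, measured at T0 and T1. Table 1 makes enhancing readiness part of MIP. The text gives the before-and-after measurement as what allows the moderator role. The Possible moderators section speaks of baseline factors, and the Moderation analysis section does not say which value enters. The T1 interaction is therefore permitted, and it conflicts with the baseline description.

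**The case against.** Several points on the other side stand.

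- **Not all mechanism analyses fail.** A reader might infer that the fidelity effect is inestimable. The documents do not support that in general: it needs complete overlap with arm, or coding of MIP sessions only, whereas the fidelity section speaks of sampling from all sessions. Under partial overlap the effect can be estimated, but weakly.
- **Overlap is an inference.** No pass rates are given, and the article does not say whether the proficiency or the competency threshold defines the variable. Its Discussion notes that MI delivery is often troublesome, so some variation within MIP is expected.
- **Missing by design.** The scored sessions are a random sample. The gap costs precision and does not of itself cause bias.
- **The T1 value is not stated outright as the moderator.** A reader might infer that it is, but the text says only that readiness is measured at both times. A T0 interaction fits the text and is valid, and the other moderators also have T0 values.
- **Mediation is planned.** A reader of the Moderation analysis section alone might infer that mechanisms are tested only by an interaction term. The Process evaluation section does plan mediation analyses, so that inference fails.
- **Deferred detail.** The handling of unscored patients and the exact mediation model may be left to a fuller document. But the choice of mediator and the 20% scoring are fixed here, and together they cause the difficulty.

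**Conclusion.** The point holds in a limited form. As stated, the fidelity mediation analysis would be uninformative: about 64% of patients have no value, and fidelity is expected to overlap strongly with arm. Under the four assumed pass-rate pairs, phi is about 0.6–0.95 and power about 8–31% with 23 to 29 scored patients per arm. The coverage figures follow from the article's own numbers, taking two sessions per patient and simple random sampling of sessions. The overlap and power figures rest on the assumed pass rates and on a 5-point effect with SD 10.

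The role and time point of readiness are worded inconsistently, and the wording permits an interaction that could not be read as effect modification.

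These are secondary analyses. The randomized comparison, the primary outcome and the sample size are not affected.

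**What to change.** - **Process evaluation (statistical analysis):** drop fidelity as mediator of the arm effect. Report it descriptively by nurse and arm, as a check on delivery and contamination. Label any fidelity–outcome association within MIP as exploratory.
- **MI-specific possible active ingredients, and Process evaluation:** name as mediators the T1 value or T0–T1 change of variables measured in both arms (MPRCQ2, TMQ, GSE, CPSS), adjusted for their T0 value and for the baseline outcome.
- **Moderation analysis:** restrict moderators to T0 values, including readiness, each tested as an arm-by-T0 interaction.
- **Leave the sampling of sessions as it is.** Drawing the 20% by patient would cut coverage from about 58 patients to 0.20 × 160 = 32.

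The cost is wording and somewhat different secondary models. Table 2 already schedules all four measures at T0 and T1, so no new data are needed. The claim that fidelity mediates the effect is given up.
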